### Study intervention

The primary aim of the REACT study is to assess the effectiveness of a community-based physical activity intervention for reducing the progression of mobility-related functional limitations in older people who are at high risk of transition from independence to mobility-related disability.

#### Intervention arm

The intervention group will receive a standardised 12-month exercise programme designed for delivery in leisure/community centres where low-cost off-peak capacity is available. REACT will be delivered by qualified exercise professionals with experience of leading exercise classes in the community. We will collaborate with existing community-based organisations who have access to suitable venues and delivery staff. Sessions will be organised as group activities with up to 15 participants per group, but there will be individually tailored elements for aerobic exercise, strength work and exercise progression plans. Activities will include cardiovascular, strength, balance and flexibility exercises and daily lifestyle-based activity in the form of neighbourhood walking and active travel. Breaks in sedentary time will also be promoted. Social activities, such as post-exercise coffee meetings and community-based activities, will be organised to encourage a ‘social club’ atmosphere, promote long-term compliance and contribute to social well-being.

The intervention sets a long-term target for participants of 150 min of moderate-intensity activity per week, which is approached progressively. ‘Home-friendly’ exercises and written materials will be supplied to encourage participation in exercise in the home environment [17]. If participants miss two consecutive sessions, REACT leaders will telephone the participant to problem-solve ways for the participant to re-engage with the programme.

One novel element is the accompanying ‘REACT ambassadors’ scheme that provides the opportunity for participants to develop expertise and contribute as a local neighbourhood coordinator, or in other volunteering roles, determined by the provider. Our aim is to produce a pragmatic model of delivery that is rooted in the needs of the local community, that attracts a diverse population of older adults, is increasingly self-sustaining, and that has potential for application across the UK.

REACT will be delivered in two progressive phases (adoption and maintenance) and established behaviour-change techniques will be used to enhance motivation, to make realistic plans for sustainable activity, to pre-empt and overcome barriers, to engage social support and to use self-monitoring and self-regulatory techniques to support the maintenance of behaviour change. The REACT co-applicants will provide training in intervention delivery methods, including detailed session plans to ensure consistency in, and fidelity to, programme delivery.

*Start up* (adoption: weeks 1–8): the purpose of this phase is to stimulate initial increases in physical activity and fitness, to reduce any anxieties or concerns about exercise, and to build confidence and a sense of attachment to the programme. Each participant will receive a 45-min individualised, face-to-face introductory session which will be used to personalise the programme for starting levels and progression. Two 60-min physical activity sessions per week, plus 15–20 min of social time, will then be delivered by the REACT trainer.

*Build up* (adoption: weeks 9–24): a 45-min interactive educational/social session run by the REACT trainers will be added at the end of one of the two weekly sessions. These sessions will use evidence-based, person-centred behaviour-change strategies to build intrinsic motivation and self-efficacy. They will be designed to maximise enjoyment, social interaction and group identity [18]. Behavioural management will focus on self-regulation using goal setting, self-monitoring, reviewing of goals and problem-solving [19, 20]. A key focus will be on exploring and planning transition to more lifestyle-based activities. Pedometers will be introduced during these sessions to support the participant in the transition to the maintenance phase. After week 12, the exercise session frequency will be reduced to one per week but with an expectation that participants find an hour per week to exercise at home, in the neighbourhood or at a physical activity session in their local community. Participants will also be introduced to the REACT Ambassador training programme which will be delivered during the maintenance stage.

*Taking charge* (maintenance: weeks 25 to 52): the maintenance stage will focus further on home and neighbourhood-based activities while continuing with a weekly centre-based physical activity session followed by a short social session. Participants will enact action plans for physical activity outside of the REACT programme that were made during the transition phase and will be supported through group social/education meetings once a month. We will encourage groups to self-organise their own social interaction beyond the scope of the study and to consider doing activities together. Participants will be informed about local opportunities for physical activity in their community.

All intervention group participants will be offered the opportunity to be trained as *REACT Ambassadors* to help support the long-term sustainability of the programme. REACT Ambassadors will primarily focus on becoming local community activators facilitating local physical activity opportunities. This will help to increase maintenance activities and increase the frequency of meetings in the maintenance stage without adding to intervention costs.

Post intervention: REACT Ambassadors will help to sustain activities after the initial 12 months by organising group meetings and activities, and participants may be offered the weekly REACT sessions at a subsidised rate (subject to agreement with providers). The Ambassador programme is, therefore, designed to promote growth and increase sustainability.

#### Control arm

After completion of baseline assessments, participants allocated to the control group will be given information regarding healthy ageing. They will be invited to three 60–90-min group sessions over the 2 years of the study. These will consist of presentations and discussion groups on various aspects of healthy ageing (excluding physical activity) and incorporate socialising opportunities.

#### Intervention delivery

The REACT intervention sessions will be delivered at leisure or community centres provided by REACT collaborators during low-usage hours in economically and ethnically diverse areas in Bath, Bristol, Devon and Birmingham. REACT trainers will be qualified to at least Register of Exercise Professionals (REPS) Level 3 (Exercise Referral Diploma or equivalent) and will be experienced in delivering safe and effective exercise sessions to older adults. Social/education sessions may be delivered by other staff from the same organisation. All staff will attend a 2-day, standardised training workshop on the delivery of the REACT exercise and social/education sessions, based on a written programme of materials and manuals.

#### Intervention fidelity

We will include a range of the strategies outlined by the NIH Behaviour Change Consortium to reinforce intervention fidelity [21]. We will: (1) ensure ‘design fidelity’ by building our intervention around a clear logic model (Additional file 3: Figure S1); (2) recruit REACT trainers with appropriate skills and experience; (3) develop an accessible, standardised intervention manual; (4) implement the standardised REACT trainer training programme; (5) train more REACT trainers than needed to accommodate illness or withdrawal; (6) monitor delivery fidelity via recording of consultation meetings for a sample of three to four sessions per intervention provider and the application of a *fidelity checklist*: and (7) check for intervention ‘receipt’ and ‘enactment’ of appropriate levels of physical activity outside of the REACT sessions by including opportunities to check participant understanding of the correct performance of exercises and regularly review progress in the social-educational sessions. In addition, fidelity will be enhanced by incorporating a gradual transition to daily activity within the structure of the REACT intervention (i.e. withdrawal of one session per week after 12 weeks, reduction of social sessions to once/month after the first 6 months, with targeted planning of ongoing lifestyle-based physical activities around each transition).

#### Intervention theoretical framework

The REACT social and educational programme draws on two overlapping and mutually compatible theoretical perspectives, Social Cognitive Theory and Self Determination Theory. These theories provide the main principles and processes for supporting behaviour change [22, 23]. The Skills for Maintenance (SkiM) model has also been used to identify additional processes and techniques to promote maintenance of physical activity [24]. For further detail see the REACT logic model (Additional file 3: Figure S1).

### Assessments

A full list of measures and time points is presented in Table 2. The person conducting the assessments will check for completion of questionnaires before participants leave the assessment premises, and will make every effort to ensure that missed or spoiled questions are addressed.

**Table 2 Tab2:** REACT schedule of assessment

Visit type	Scr1^1^	Scr2^2^	FU3^3^	FU4^4^	FU5^5^
Visit code		SV1	F06	F12	F24
Visit number		1	2	3	4
Telephone call	1				
Activity/assessment month	− 0.5	0	6	12	24
Form name					
Verbal consent	X				
Telephone screening (some elements of inclusion and exclusion criteria) (see Additional file 4)	X				
Written informed consent (see Additional file 5)		X			
Contact information update	X	X	X	X	X
Demographic, social, economic	X				
SPPB battery (see Additional file 6 for full CRF) [12]		X	X	X	X
Accelerometry		X	X	X	X
Height and weight		X		X	X
MoCA – Montreal Cognitive Assessment [13]		X	X	X	X
PASE questionnaire [14]		X	X	X	X
Dynometer (hand-grip strength)		X	X	X	X
Ageing Well profile (two sites full scale, one site social well-being scale only) [15]		X		X	X
Health-related quality of life (EQ-5D-5 L, SF-36) [16, 17]		X	X	X	X
Sleep Condition Indicator [18]		X		X	X
Pain (Western Ontario and McMaster Universities Osteoarthritis Index (WOMAC) [19]		X		X	X
Mobility Assessment Tool-short form (MAT-sf) [20]		X	X	X	X
Cognitive function (UK Biobank Healthy Minds Questionnaire) [21]		X	X	X	X
Medical history including medications, chronic diseases, cardiovascular disease and other conditions		X			
Falls Inventory including falls in last 6 months and injuries relating to falls		X	X	X	X
Health and Social Service Usage including use of primary, secondary or community care services in previous 6 months		X	X	X	X
*(MRI sub-study)* MRI scan, detailed cognitive assessment and gait analysis		X	X	X	
Process evaluation^6^			X	X	
Session attendance (intervention group only)			X	X	
Total contact time for each participant		X	X	X	
Physical activity related self-concept			X	X	X
Perceived tension of maintaining current PA			X	X	X
Perceived tension of maintaining current exercise		X	X	X	X
Autonomy in relation to PA		X	X	X	X
Competence for PA		X	X	X	X
Relatedness for PA		X	X	X	X
Enjoyment of PA		X	X	X	X
Perceived intrinsic benefits of PA (social, physical and emotional)					
Autonomy for strength-building exercise		X	X	X	X
Competence for strength-building exercise		X	X	X	X
Relatedness for strength-building exercise		X	X	X	X
Enjoyment of strength-building exercise		X	X	X	X
Perceived intrinsic benefits of strength-building exercise (social, physical and emotional)		X	X	X	X
Enjoyment of the REACT programme (intervention group)			X	X	
Credibility/identification with the session facilitators (intervention group only)			X	X	

^1^Telephone screening, ^2^Face-to-face screening (baseline assessment), ^3^6-month follow-up, ^4^12-month follow-up, ^5^24-month follow-up. ^6^Bespoke or adapted questionnaire developed for the REACT study. Full details of the process evaluation will be reported in detail elsewhere. The questionnaires are provided in Additional file 6

Abbreviations: *CRF* Case Report Form, *MRI* magnetic resonance imaging, *PA* physical activity, *SPPB* Short Physical Performance Battery test

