## Methods

### Trial design

The study protocol is presented in accordance with the Standard Protocol Items: Recommendations for Interventional Trials (SPIRIT) guidelines (Additional files 1 and 2).

The REACT study is a multi-centre, pragmatic, two-arm, parallel-group randomised controlled trial with an internal pilot phase and that incorporates comprehensive process and economic evaluations. Following identification and recruitment, 768 participants who meet the study inclusion criteria will be randomised to receive either the REACT intervention, delivered over a period of 12 months by trained facilitators or a minimal control intervention. The pilot phase will assess the feasibility of recruitment methods (allowing for some refinement if needed) and confirm adequate retention rates in the intervention and the study, prior to progressing with the main trial. A nested sub-study, led by the Wellcome Centre for Integrative Neuroimaging, University of Oxford, employing magnetic resonance imaging (MRI), will test the hypothesis that the REACT intervention will slow the rate of brain atrophy and of decline in cognitive function. Outcome data will be collected at baseline, 6, 12 and 24 months for the main study, with MRI sub-study data collected at baseline, 6 and 12 months. The REACT study was reviewed and approved by the National Health Service (NHS) South East Coast-Surrey Research Ethics Committee (15/LO/2082). The study is registered as a current randomised controlled trial (ISRCTN45627165).

The REACT study will be conducted at three UK sites – Bath/Bristol, Devon and Birmingham – allowing recruitment of a socio-economically and ethnically diverse sample including participants from urban, rural and semi-rural locations.

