### Economic evaluation

The economic evaluation will estimate the cost-effectiveness of the REACT intervention compared to control, for older people with major mobility limitations, from the perspective of the NHS and Social Care Services.

Using data collected within trial we will estimate the resource use and costs associated with delivery of the intervention, and the wider NHS-, social care- and participant-level resource use and costs over a 24-month follow-up. The primary component of resource use for delivery of the intervention is the time input (contact and non-contact time) for REACT trainers, and data will be collected on each activity by the trainer over the delivery of the intervention for each group, and across each phase of intervention delivery. Other areas of resource use (e.g. training, set-up, facility costs, cost of pedometers) will be recorded within trial by the trial coordinator. Data on use of health-, social care- and other participant-related resource use will be collected, using a participant self-report resource use questionnaire, at baseline, 6, 12 and 24 months. Data on resource use will be combined with national unit cost data obtained from available sources including Personal Social Services Research Unit (PSSRU) and NHS reference costs to estimate costs over the 24-month follow-up [26, 27]. The primary economic outcome measure will be the quality-adjusted life years (QALYs) derived from participant-reported EuroQoL five-dimension, five- level (EQ-5D-5 L) data, applying the area-under-the-curve approach [28], collected alongside the resource use questionnaire and using the UK tariff (presently recommended by NICE [29]). Data on estimated costs and QALYs by group will be presented, together with incremental QALYs and incremental costs, to present a policy-relevant cost-effective analysis (CEA).

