Analysis will follow established methods for the conduct of economic evaluation in health technology assessment [30] and will be consistent with recommendations from NICE (UK) on ‘reference case’ cost-effectiveness analyses [31]. Findings will be reported in keeping with the CHEERS guidelines for cost-effectiveness studies [32]. CEA will be presented using base case estimates and uncertainty will be considered via detailed one-way and multi-way sensitivity and scenario analyses. The non-parametric nature of the distribution of resource use and cost data will be addressed using bootstrapping methods for estimation of confidence intervals around estimates of mean costs and incremental cost-effectiveness ratios (ICER). Results will include disaggregated data, as well as synthesis of costs and outcome data, and will include presentation of cost-effectiveness plane and cost-effectiveness acceptability curves to describe the likelihood of cost-effectiveness at different cost-effectiveness thresholds [33, 34].

To address missing data on costs and outcomes, multiple imputation will be used for making the assumption that the data are missing at random [35]. Given the longer-term nature of potential benefits from the REACT intervention, we will conduct evidence synthesis and decision-analytic modelling to assess the longer-term (lifelong) consequences of the intervention vs. control, including consequences in terms of health and social care costs.

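### With the 6-month recall shown in Table 2, self-reported service use covers 18 of the 24 months to be costed, and no rule is given for months 12 to 18

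*Protocol article*

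**What the plan says.** Three statements in the protocol article bear on this.

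- **Recall period.** Table 2 (Assessments) has one row for the service-use form: "Health and Social Service Usage including use of primary, secondary or community care services in previous 6 months". The row is marked at the baseline, 6-, 12- and 24-month visits. No different look-back is shown for month 24.
- **Timing.** The Economic evaluation section says these data are gathered "using a participant self-report resource use questionnaire, at baseline, 6, 12 and 24 months". Trial design gives the same schedule: "Outcome data will be collected at baseline, 6, 12 and 24 months for the main study". No 18-month contact appears anywhere.
- **Costing period.** The Economic evaluation section says the trial data will be used to estimate "wider NHS-, social care- and participant-level resource use and costs over a 24-month follow-up". It later says unit costs will be applied "to estimate costs over the 24-month follow-up".

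For gaps in cost and outcome data, the same section states that "multiple imputation will be used for making the assumption that the data are missing at random". It gives no rule for interpolating or extrapolating service use, and mentions no linkage to routine records.

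**The concern.** A 6-month recall suits visits 6 months apart. It fits months 6 and 12, but the last interval is 12 months long, and a 6-month recall at month 24 reaches back only to month 18. The stated recall, visit times and costing period therefore do not fit together.

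Cost-effectiveness is one of the trial's two headline aims. Months 12-18 are the first half-year after the 12-month programme ends, when any change in service use that outlasts the programme would begin to show. A 24-month cost that leaves this period out, or fills it by a rule chosen after the data are seen, weakens the incremental cost and the cost-effectiveness ratio built on it.

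**Working it through.** **Inputs**
- Visits at months 0, 6, 12 and 24 (Trial design; Table 2; Economic evaluation).
- Recall of 6 months at each visit (Table 2).
- Costing period of 24 months (Economic evaluation).

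**Step 1: coverage.** A form completed at month *v* with a 6-month recall covers the interval from *v* − 6 to *v*.

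| Visit (month) | Window covered | Follow-up months |
|---|---|---|
| 0 | −6 to 0 (before randomisation) | 0 |
| 6 | 0 to 6 | 6 |
| 12 | 6 to 12 | 6 |
| 24 | 18 to 24 | 6 |

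Total: 6 + 6 + 6 = 18 months. The plan's figure of 24 months is not reproduced.
- Covered: 18/24 = 75%.
- Not covered: months 12 to 18, which is 6/24 = 25% of follow-up and 6/12 = 50% of the post-intervention year.

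**Step 2: effect if the windows are simply summed.** Let service cost accrue at a constant rate *r* per month in one arm. The true total is 24*r* and the sum of the windows is 18*r*, so the shortfall is (24*r* − 18*r*)/24*r* = 25%. With a constant between-arm difference *d* per month, the incremental service cost is 18*d* instead of 24*d*, again 25% short. If the rate is not constant, the error in the incremental cost is whatever difference arises in months 12-18, and the document gives no figure from which to bound it.

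**Step 3: comparison with QALYs.** Table 2 schedules EQ-5D-5L at months 0, 6, 12 and 24, and the plan uses the area under the curve. Joining the month-12 and month-24 values gives that year a contribution of (u12 + u24)/2 × 1 year. QALYs therefore span all 24 months by a stated rule. Costs have no corresponding rule.

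**Step 4: can the planned imputation fill the gap?** Multiple imputation under missing at random learns from participants whose value is observed. Here a months 12-18 value is observed for nobody, so the data cannot inform a model for it. Filling it needs an explicit assumption.

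**Step 5: coverage after a change.** With a 12-month look-back at month 24, that window becomes 12 to 24, and coverage is 6 + 6 + 12 = 24 of 24 months.

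**Step 6: one explicit assumption, if the 6-month form stays.** Write C(a-b) for the service cost in months a to b. Interpolation sets C(12-18) = [C(6-12) + C(18-24)]/2. At a constant half-yearly cost *c*, the total becomes 3*c* + *c* = 4*c*, the full 24 months. The result is only as good as the assumption that use in the unobserved half-year lies midway between its neighbours.

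**The case against.** **The form itself is not shown.** The evidence is one row label shared by four visits and worded as a summary. The questionnaires are in an additional file that is not at hand. A reader might infer that months 12-18 will certainly go unobserved; the document does not support that, because a longer look-back on the actual month-24 form cannot be excluded. What stands is that the article states a 6-month recall and a 24-month costing period, and these conflict. If the form differs, Table 2 needs correcting.

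**An article condenses, and a health-economics plan may hold the rule.** This is fair for the method of estimation. The article also plans sensitivity and scenario analyses. A reader might infer that the cost-effectiveness ratio will set 24 months of QALYs against 18 months of service costs. That follows only if the windows are summed without adjustment, which the article does not say. Even so, the point does not rest on silence: the stated recall, visit times and horizon are inconsistent.

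**QALYs are interpolated over the same year.** This is true, and costs could be handled in a similar way. But the QALY rule is stated and the cost rule is not.

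**Delivery costs are captured separately.** This stands. Trainer time and other delivery resources are recorded within the trial, so the gap concerns participant-reported use only.

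**Falls and session attendance.** The falls row, "Falls Inventory including falls in last 6 months and injuries relating to falls", has the same gap. A reader might infer that a 24-month falls total is compromised, but no such total is promised. The only analysis in the article that names falls is the subgroup defined by the 6 months before baseline, which this recall serves. A reader might also count the end of attendance recording at month 12 as a second gap. The programme lasts 12 months, so that is consistent, and later sessions are only a possibility: "participants may be offered the weekly REACT sessions at a subsidised rate (subject to agreement with providers").

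**Conclusion.** The point holds as an inconsistency between the service-use recall in Table 2 and the costing period in the Economic evaluation section. On the stated schedule, 18 of 24 follow-up months are covered; months 12-18 are not, and the planned imputation does not supply them. These coverage figures need only the stated visit times and recall.

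The 25% understatement of service cost, and of any incremental service cost, is conditional. It requires that the three windows be summed as the 24-month total and that use accrue at a constant rate.

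A reader might also infer that half of any year-2 cost difference would be lost. The documents do not support that as a limit: half is the share of time, and the share of the difference could be anything from none to all of it.

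The gap should be resolved before the economic analysis, but it does not touch the primary outcome, SPPB at 24 months, and is not a fault that the main comparison depends on.

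**What to change.** 1. **Check the month-24 service-use form.** If it already asks for more than 6 months, correct Table 2 and nothing else is needed.
2. **If it asks for 6 months, reword the month-24 look-back** to cover the time since the 12-month assessment. Enrolment began in March 2016, so 24-month visits start around March 2018, and final assessments are expected by the end of November 2019. The cost is one reworded form and a minor amendment. The drawback is a 12-month recall, which is less accurate than a 6-month one.
3. **Where the 6-month form is kept or has already been used, pre-specify how months 12-18 are estimated**, for example by interpolating between the 6-12 and 18-24 month rates. Add a sensitivity analysis with other assumptions, such as applying the 18-24 month rate alone. State that this step is separate from the multiple imputation for participants who miss a form. The cost is a short paragraph in the economic analysis plan.

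The falls form needs the same change only if a cumulative 24-month falls count is wanted.
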